**Brain MR imaging**		
Required sequences	T1-weighted imaging T2-weighted imaging Fluid-attenuated inversion recovery (FLAIR) Diffusion-weighted imaging (DWI) Gradient echo T2*-weighted imaging (or susceptibility-weighted imaging [SWI])	
**Carotid plaque MR imaging**		
Required sequences	3D time of flight (TOF) 3D magnetisation-prepared rapid gradient-echo (MPRAGE) or an equivalent sequence that allows identification of intraplaque haemorrhage	
Optional sequences^a^	3D with contrast	Pre- and post-contrast T1-weighted SPACE/CUBE/VISTA imaging
	2D with contrast	Pre- and post-contrast black blood T1-weighted imaging
	3D without contrast	T1-weighted and T2-weighted black blood SPACE/CUBE/VISTA imaging
	2D without contrast	Black blood T1-weighted imaging T2-weighted imaging

^a^The option is given to use intravenous gadolinium contrast. It is preferred to use 3D imaging however there is an option for 2D imaging

#### Carotid plaque imaging

MRI is far superior to computed tomography (CT) in identifying the different components of a carotid plaque, in particular IPH. Several carotid plaque MRI protocols are summarised in a recent white paper [34]. Centres are given flexibility to choose their preferred plaque imaging protocol according to their local expertise from within a limited number of sequences varying in complexity and performed with or without the use of gadolinium-based contrast medium (Table 2). The basic protocol, which is well suited for demonstrating IPH, requires two sequences: 3D time of flight (TOF) and 3D magnetisation-prepared rapid gradient-echo (MPRAGE) or an equivalent MRI sequence that allows visualisation of IPH. This minimum requirement could be implemented at any centre using a standard head-and-neck coil on a 1.5 or 3.0 Tesla system, although the latter is preferable. The sequences of the basic protocol will allow quantification of stenosis, as well as detection of plaque ulceration, calcification and IPH [34]. Ulcerations will be scored on contrast-enhanced MR angiography, alternatively on 3D TOF, or, if unavailable, any other sequence that allows identification of plaque ulceration. Plaque ulceration is defined as an intimal defect larger than 1 mm in width [35]. IPH is identified as a hyperintense region (compared to the sternocleidomastoid muscle) in the bulk of the plaque on MPRAGE or if unavailable, TOF images or any other sequence that allows identification of IPH [34, 36].

More advanced sequences that have been designed to image plaque burden, the status of the fibrous cap and the size of lipid-rich necrotic core, based on recent expert consensus recommendations, are optional [34]. A thin or ruptured fibrous cap is defined as an interrupted region of signal enhancement adjacent to the lumen on the post-contrast images overlying the lipid-rich necrotic or full absence of a region with signal enhancement adjacent to the lumen overlying the lipid-rich necrotic core [34, 37]. A quality score is used to indicate the certainty on the score. A lipid-rich necrotic core is identified as an area in the bulk of the plaque that is hyperintense on the T1-weighted black blood MR images, does not enhance on the post-contrast T1-weighted black blood images, and potentially is hypointense in the same region on T2-weighted MR images.

#### Duplex ultrasound

Carotid duplex ultrasound will be performed at baseline and annually to estimate the percentage diameter reduction and grading of stenosis of the carotid artery on the randomised side and on the contralateral side. The degree of stenosis will be determined in the central trial office based on the peak systolic velocities of the common carotid and the internal carotid arteries and the end diastolic velocity of the internal carotid artery, on the basis of predefined, standardised flow velocity criteria, which equate well with the severity of carotid stenosis measured on catheter angiography using the NASCET method [38, 39].

### Participant timeline {13}

Table 3 summarises the timing of baseline and follow-up visits and investigations given in the protocol. Prior to randomisation, the following investigations are required: routine serum investigations, electroca rdiogram, imaging of both carotid bifurcations showing the severity of stenosis bilaterally and brain MRI. If MR is contra-indicated or not available within a reasonable time period for any reason, brain CT should be done instead. Baseline data will be collected at randomisation and includes the mRS assessed by using the Rankin Focused Assessment (RFA). Patients also complete the European Quality-of-Life 5 Dimension Questionnaire (EQ-5D) [40] at baseline and the MoCA [41]. Patients are followed up by a neurologist or stroke physician, or a clinician/research practitioner under the close supervision of a neurologist or stroke physician. Required investigations during follow-up include at least annual measurements of the blood pressure and serum cholesterol and an annual carotid duplex ultrasound. Brain MRI is required at the time of randomisation and at 2 and 5 years after randomisation to determine the rate of the MR-based outcome events, unless contra-indicated. Additional brain MRI is required whenever a suspected stroke or a TIA occurs during the study period to confirm the clinical diagnosis. In patients with contraindications for MRI or if MRI was not available within a reasonable period, brain CT is allowed instead. MRI of the carotid plaque is also done prior to randomisation at centres able to perform the required sequences.

**Table 3 Tab3:** Outline of baseline and follow-up appointments including investigations required and target time window

Visit/follow-up	Investigations	Target time window
Baseline	Brain MRI	14 days in symptomatic stenosis or 28 days in asymptomatic stenosis before or after randomisation, done before any revascularisation procedure
	Initial carotid imaging	120 days before randomisation up to the day of randomisation
	Confirmatory second carotid imaging	14 days before randomisation up to the day of randomisation
	Clinical assessment, blood pressure Baseline blood lipids and glucose, serum troponin levels ECG MoCA, EQ-5D, RFA	14 days before randomisation up to the day of randomisation
Post-procedure visit in revascularised patients only	Clinical assessment, blood pressure Troponin and ECG	Day of treatment +48 h ±24 h
4–6 weeks post-randomisation	Clinical assessment, blood pressure MoCA, EQ-5D, RFA	Day of treatment +30 days ±7 days in revascularised patients
	ECG and troponin in the OMT arm	Day of randomisation +42 days ±7 days in OMT only patients
	Carotid ultrasound in revascularised patients	Day of treatment +30 days ±7 days
	Brain MRI (optional)	Day of treatment +30 days ±7 days in revascularised patients Day of randomisation +42 days ±7days in OMT only patients
3 months post-randomisation	Telephone follow-up	Day of randomisation +90 days ±14 days
6 months post-randomisation	Clinical assessment, blood pressure EQ-5D, RFA Fasting lipids and glucose	Day of randomisation +180 days ±14 days
Annual follow-up	Clinical assessment, blood pressure EQ-5D, RFA Fasting lipids and glucose Carotid ultrasound MoCA and brain MRI at 2 and 5 years	Day of randomisation +X years ±1 month
Bi-annual telephone follow-up	Telephone follow-ups between annual follow-ups	Day of randomisation +X years +6 months ±1 month

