**Methods:**

Patients are randomised between immediate revascularisation plus OMT versus OMT alone. Suitable patients are those with asymptomatic or symptomatic carotid stenosis ≥50% with an estimated 5-year risk of stroke of <20%, as calculated using the Carotid Artery Risk score. MRI of the brain at baseline and during follow-up will be used as a blinded measure to assess the incidence of silent infarction and haemorrhage, while carotid plaque MRI at baseline will be used to investigate the hypotheses that plaque characteristics determine future stroke risk and help identify a subgroup of patients that will benefit from revascularisation. An initial analysis will be conducted after recruitment of 320 patients with baseline MRI and a minimum of 2 years of follow-up, to provide data to inform the design and sample size for a continuation or re-launch of the study. The primary outcome measure of this initial analysis is the combined 2-year rate of any clinically manifest stroke, new cerebral infarct on MRI, myocardial infarction or periprocedural death.

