##### Revascularisation

Patients allocated to revascularisation will have CEA (or in selected cases CAS, if considered preferable to CEA by local investigators) as soon as possible after randomisation and not later than 2 weeks for symptomatic patients or 4 weeks for asymptomatic patients, in addition to OMT. It is anticipated that the majority of patients allocated to revascularisation will be treated by endarterectomy. Detailed guidance is available to centres concerning relative and absolute contraindications to performing CAS in the trial.

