### Statistical methods

#### Statistical methods for primary and secondary outcomes {20a}

The primary analysis will be by intention-to-treat; i.e. patients will be analysed by their randomly allocated group despite what treatment they actually receive. A per-protocol analysis will be performed as an indicator of the actual treatment effect, excluding (i) patients randomised in the OMT group who undergo revascularisation within 6 weeks of randomisation without prior symptoms, as well as (ii) patients randomised in the revascularisation group who do not undergo revascularisation within 6 weeks of randomisation.

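### The baseline brain MRI is required before randomisation in the text but allowed up to 14 or 28 days after it in Table 3, which can hide early silent infarcts and, if it biases at all, favours OMT.

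*Protocol article*

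**What the plan says.** All three statements on the timing of the scan stand in the protocol article under Participant timeline {13}.

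- The text begins "Prior to randomisation, the following investigations are required", and the list that follows includes "imaging of both carotid bifurcations showing the severity of stenosis bilaterally and brain MRI".
- Later in the same paragraph: "Brain MRI is required at the time of randomisation and at 2 and 5 years after randomisation to determine the rate of the MR-based outcome".
- Table 3, Baseline, Brain MRI: "14 days in symptomatic stenosis or 28 days in asymptomatic stenosis before or after randomisation, done before any revascularisation procedure".

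The other baseline rows of Table 3 close on the day of randomisation. The clinical assessment row, for example, reads "14 days before randomisation up to the day of randomisation". The allowance after randomisation is particular to the brain MRI.

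Under Revascularisation, the procedure is to be done "as soon as possible after randomisation and not later than 2 weeks for symptomatic patients or 4 weeks for asymptomatic patients". Section {17a} says that patients and clinicians are not blinded, and that follow-up scans are read blind to treatment. Outcomes {12} makes new cerebral infarct on MRI a component of the 2-year primary outcome of the initial analysis.

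**The concern.** The baseline scan is the reference for the MRI component of the outcome. If it is taken after randomisation, a silent infarct that arose in between is already present on it and cannot be recognised as new at 2 years.

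The interval in which this can happen differs by arm. After allocation to revascularisation, the scan must come before a procedure that is to be done early, so the interval is cut short. After allocation to OMT alone, it can run to the full 14 or 28 days. Staff who know the allocation arrange the scan, so blinded reading of follow-up scans does not remove the difference.

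Any net effect takes events from the OMT arm, which is the arm to be shown non-inferior. An error in that direction makes a non-inferiority conclusion easier to reach.

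**Working it through.** **Inputs from Sample size {14}.** OMT stroke rate at 2 years 3%. OMT stroke or silent infarct 9%, hence 9% − 3% = 6% silent. Composite rates 11% (OMT) and 18% (revascularisation). Margin 4 points. 157 per arm, 80% power. The article states no alpha; one-sided 0.025 is assumed.

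**The plan's own figure.** The distance to the margin is 0.04 − (0.11 − 0.18) = 0.11. The variance term is 0.11 × 0.89 + 0.18 × 0.82 = 0.2455. Then n per arm = 0.2455 × (1.960 + 0.842)² / 0.11² = 159.2, so 160 per arm and 320 in all. This is within 3% of the stated 157 and 314. Power at 157 per arm is 79.4%. The timing conflict does not affect this calculation.

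**What can be hidden.** A clinical stroke after randomisation still counts through the clinical component, whatever the baseline scan shows. Only the 6% silent share is exposed. With a scan delay of d days and early risk k times the 2-year average (k is an assumption):

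hidden share = 6% × d / 730.5 × k

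The type I error column takes true rates at the margin (22% on OMT, 18% on revascularisation) and 157 per arm. It gives the chance of declaring non-inferiority once the OMT rate is lowered by the hidden share h: Φ[(0.04 − (0.22 − h − 0.18))/SE − 1.96] = Φ[h/SE − 1.96], with SE = √{[(0.22 − h)(0.78 + h) + 0.18 × 0.82]/157}.

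| d (days) | k | Hidden (points) | Patients per 157 | One-sided type I error (nominal 0.025) |
|---|---|---|---|---|
| 14 | 1 | 0.12 | 0.2 | 0.027 |
| 28 | 1 | 0.23 | 0.4 | 0.028 |
| 14 | 3 | 0.34 | 0.5 | 0.030 |
| 28 | 3 | 0.69 | 1.1 | 0.036 |
| 14 | 5 | 0.57 | 0.9 | 0.034 |
| 28 | 5 | 1.15 | 1.8 | 0.044 |

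These are upper bounds. Each row supposes that every OMT patient is scanned on the last allowed day and that nothing is hidden in the other arm.

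**Netting between arms.** Before the procedure, a late scan hides silent infarcts in the revascularisation arm too. If early risk is the same in both arms until the procedure, only the difference in delay matters. With OMT scans at day 28 and revascularisation scans at day 14, for illustration, the net effect under even accrual is 6% × (28 − 14) / 730.5 = 0.12 points, half the 28-day bound.

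**The case against.** Much can be said for Table 3. Its condition that the scan come before any procedure prevents a larger error, that of filing procedural infarcts as baseline. Its limits of 14 and 28 days match the procedure deadlines of 2 and 4 weeks, so late scans hide silent infarcts in both arms. Under even accrual the effect is well under one patient per arm. The larger rows of the table need early risk to be concentrated, and the 28-day window applies only to asymptomatic stenosis, for which the section on the CAR score assumes a 5-year risk of at most 5%. DWI is mandatory, so acute lesions on a late scan can be recognised. Detailed reading rules may stand in the analysis plan or the full protocol, which are not shown. All of this stands. It limits the size of the effect, but it does not resolve the conflict between the text and the table.

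A reader might infer more than the documents support, in two ways.

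- **That the bias could use up more than half of the margin.** This would come from applying the calculation to the whole 9% and placing a large share of events in the first weeks. Clinical strokes are not hidden, so the base is 6%. Even if a quarter of silent infarcts fell within 4 weeks, which nothing in the documents supports, the bound would be 6% × 0.25 = 1.5 points, or 37.5% of the margin.
- **That the plan contradicts intention-to-treat, because patients operated on before their scan drop out of the analysis.** The Abstract says that the initial analysis takes place "after recruitment of 320 patients with baseline MRI". That describes when the analysis is done and is not an exclusion rule. Section {20a} states "The primary analysis will be by intention-to-treat", and its only exclusions belong to the per-protocol analysis. Participant timeline {13} also allows CT where MRI is contraindicated or not available in reasonable time. No passage removes such a patient.

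**Conclusion.** The point holds as a conflict within one section, with a possible bias of modest size. The text places the baseline brain MRI before or at randomisation, and Table 3 allows it up to 14 or 28 days after an open allocation. If Table 3 is followed, early silent infarcts can be filed as old in both arms. The exposure can be longer on OMT, so the net bias, if there is one, favours non-inferiority.

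Even accrual makes the effect negligible. It becomes noticeable only if early risk is several times the average and many OMT scans are late. The 3- to 5-fold multiplier is an assumption, as is the one-sided 0.025. The documents give neither the early risk nor the number of late scans, so whether the bias is real can be settled only from the scan dates.

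**What to change.** 1. Reconcile the text and Table 3 so that the plan states one timing rule for the baseline brain MRI.
2. For baseline scans taken after randomisation, classify acute DWI lesions not attributable to the qualifying event as post-randomisation infarcts, with these scans read blind to allocation.
3. Report by arm the number of baseline scans that were late or missing, and the days from randomisation to scan.
4. Add a sensitivity analysis limited to patients whose baseline scan was done on or before the day of randomisation.

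Randomisation is suspended, DWI is a mandatory sequence, and images are sent to the central trial office. The change is therefore one of wording, scan dates and some re-reading, with no new scans. Its price is that the sensitivity analysis is smaller and less precise, and that attributing a DWI lesion to the qualifying event needs some judgement.

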### Sample size {14}

We expect a rate of stroke in the OMT arm of approximately 3% at 2 years after randomisation. Silent ischaemic infarcts on MRI seem to occur at twice the frequency of clinically manifest strokes [42, 43]. Thus, we expect about 9% of patients on OMT to experience clinically manifest stroke or have silent new ischaemic infarct on MRI after 2 years of follow-up. In those allocated to revascularisation, we expect a peri-operative risk of stroke of 3% and a subsequent 2-year risk of stroke of 2%. Thus, we expect about 15% of patients in the revascularisation arm to experience clinically manifest stroke or have silent new ischaemic infarct on MRI after 2 years of follow-up.

The rate of clinically manifest periprocedural myocardial infarction (MI) in carotid revascularisation is about 1% [44]. The 2-year risk of non-periprocedural MI is expected to be about 2% using the Framingham model [45] based on the characteristics of patients in the International Carotid Stenting Study (ICSS) [46]. We therefore estimated a total 2-year risk of MI of 3% in patients randomised to revascularisation and 2% in those randomised to OMT. The periprocedural death rate (unrelated to MI or stroke) in ICSS patients undergoing CEA was 0.1%. The rate of the primary outcome event in ECST-2 of clinically manifest stroke, new ischaemic infarct on MRI, MI or periprocedural death at 2 years was therefore estimated at 11% in the OMT arm alone and 18% in the revascularisation arm. Assuming these outcome event rates, 314 patients (157 in each arm) provide 80% power to demonstrate that OMT is non-inferior to OMT plus revascularisation with a non-inferiority margin of 4%. Allowing for a dropout of 15% of patients missing their 2-year MRI, we plan to recruit 360 patients for the MRI-based analysis.

We originally calculated a sample size of 2000 patients for the full ECST-2 trial, details of which can be found in the trial protocol. The sample size calculation for the continuation or re-launch of the study will be based on the outcome rates determined in the initial analysis.

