Previous trials of CEA versus medical therapy assessed only clinically manifest stroke reported by the patient and confirmed by adjudication in line with the definition of stroke as symptoms likely to be of cerebrovascular origin lasting at least 24 h. However, brain magnetic resonance imaging (MRI) is much more sensitive than clinical assessment in detecting ischaemic brain infarcts. Silent brain infarcts on MRI were found in 8% of participants in the Rotterdam study [12] and developed in 20% of participants after 10 years of follow-up in the Atherosclerosis Risk in Communities Brain Magnetic Resonance Imaging Study [13]. Silent infarcts on MRI are also seen after revascularisation procedures [14–17]. MRI can detect cerebral infarcts in the absence of clinical signs and symptoms and approximately doubles the number of episodes of cerebral infarction (clinically manifest and silent stroke) detected during follow-up. Thus, incorporation of new infarcts on brain MRI as an outcome measure is more sensitive than clinical assessment and therefore reduces the sample size required to demonstrate significant differences in the outcome between the two treatments. Another advantage of using MRI to assess outcome after stroke is that the determination of outcome is more objective than clinical assessment and outcome assessment can be done independently and blind to treatment and patient characteristics, unlike clinical assessment.

Furthermore, MRI is able to detect structural features of plaque instability, such as intra-plaque haemorrhage (IPH), which may improve the identification of patients benefitting from carotid revascularisation. The presence of IPH increases the risk of stroke in patients with carotid stenosis by a factor of more than ten and predicts risk independently of the degree of stenosis [18].

These considerations argued for a new trial to investigate the role of revascularisation in the setting of improved medical therapy adjusted to targets for risk factor control, i.e. optimised medical therapy (OMT), and using brain MRI to determine outcome measures. We therefore organised the Second European Carotid Surgery Trial (ECST-2).

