### Interventions

#### Explanation for the choice of comparators {6b}

ECST and NASCET were completed over 20 years ago and since then medical therapy has improved significantly. The widespread use of statins, lower targets for blood pressure control and more effective and promptly started antithrombotic therapy have been shown to lower the incidence of recurrent stroke in prospective registries and trials of stroke prevention [20, 21]. There has been a fall in the proportion of smokers, reduction in baseline cholesterol and blood pressure levels and increased use of dual antiplatelet therapy after stroke or TIA [22, 23]. Subgroup analyses from randomised controlled trials and case-control studies have shown that statins lower the risk of stroke in patients with cerebrovascular disease by about a third and halve the numbers requiring CEA [24–27]. Systematic reviews have consistently shown a reduction in the average rates of ipsilateral stroke in patients with asymptomatic stenosis treated medically to as low as 1% per annum [28, 29]. There is also evidence that OMT with intensive risk factor control and adjustment of medical treatments to target, the annual risk of stroke associated with asymptomatic stenosis might be lowered to 0.6% per annum [30].

Coincidently with the improvement in medical management, there has also been a reduction in the operative risks of CEA since the time of the first trials, with most contemporary databases recording rates of perioperative stroke risk less than 2% in symptomatic patients [31–33]. Given the reductions in perioperative stroke risk and stroke risk with medical therapy alone since ECST, NASCET and ACST, the indications for carotid revascularisation are no longer clear. The data suggest that many patients in whom carotid revascularisation is recommended in line with guidelines based on the old trials may be receiving CEA without benefit and with a risk of harm. It is therefore very relevant to establish whether these patients should have OMT as the intervention of first-choice in the future.

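### The sample size triples the clinical stroke rate to allow for silent infarcts, while the background says MRI only doubles it; under doubling the stated 80% power is about 75%

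*Protocol article*

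**What the plan says.** Protocol article, Sample size {14}, builds the 2-year composite in steps.

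- **OMT stroke:** "We expect a rate of stroke in the OMT arm of approximately 3% at 2 years after randomisation".
- **Silent infarcts:** "Silent ischaemic infarcts on MRI seem to occur at twice the frequency of clinically manifest strokes", supported by two references. Hence "we expect about 9% of patients on OMT to experience clinically manifest stroke or have silent new ischaemic infarct on MRI".
- **Revascularisation arm:** perioperative stroke of 3% plus later stroke of 2%, hence "we expect about 15% of patients in the revascularisation arm to experience clinically manifest stroke or have silent new ischaemic infarct on MRI".
- **Other components:** myocardial infarction (MI) adds 2% on OMT and 3% with revascularisation. Periprocedural death adds 0.1%.
- **Result:** 11% against 18%. With a 4-point margin, 157 per arm is said to give 80% power for non-inferiority of OMT.

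Background and rationale {6a} gives a different ratio. There, MRI "approximately doubles the number of episodes of cerebral infarction (clinically manifest and silent stroke) detected during follow-up", and the article uses this to argue that counting MRI infarcts lowers the required sample size.

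Explanation for the choice of comparators {6b} describes current endarterectomy practice, with "most contemporary databases recording rates of perioperative stroke risk less than 2% in symptomatic patients". The same section also reports that stroke on medical treatment in asymptomatic stenosis has fallen to about 1% a year or lower.

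**The concern.** The two statements about MRI describe the same quantity: how many infarcts are found when silent ones are added to clinical strokes. The background puts the total at about twice the clinical count, which is one silent infarct per stroke. The sample size section puts silent infarcts alone at twice the clinical count, which makes the total three times. Both are design statements, since one justifies the choice of outcome and the other sets the number of patients.

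The choice affects power in one direction. Clinical stroke is assumed to be 2 points higher with revascularisation (5% vs 3%), and the multiplier scales that gap: 6 points under tripling, 4 under doubling. The gap is the assumed advantage of OMT, and it supplies most of the distance to the 4-point margin. A larger multiplier therefore makes non-inferiority look easier to show. If the background ratio is nearer the truth, an inconclusive result is likelier than the stated 80% suggests. A re-launch planned on the same unreconciled ratio would carry the problem forward.

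**Working it through.** **Inputs** (all from Sample size {14} except the second multiplier): OMT stroke 3%; revascularisation stroke 3% + 2% = 5%; MI 2% and 3%; periprocedural death 0.1%; margin 4 points; 157 per arm. Multiplier k = 3 (Sample size {14}) or k = 2 (Background and rationale {6a}). The article states no alpha. One-sided 2.5% is inferred because it reproduces the stated size.

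**Formulas**

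- OMT rate: pO = 3% × k + 2%
- Revascularisation rate: pR = 5% × k + 3% + 0.1%
- SE = √{[pO(1 − pO) + pR(1 − pR)] / n}
- Power = Φ[(pR − pO + 0.04)/SE − 1.96]
- n per arm for 80% power = (1.960 + 0.842)² × [pO(1 − pO) + pR(1 − pR)] / (pR − pO + 0.04)²

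**Step 1: reproduce the plan (k = 3).** pO = 9% + 2% = 11%; pR = 15% + 3.1% = 18.1%. The variance sum is 0.0979 + 0.1482 = 0.2461, so SE at 157 per arm is 0.0396. The distance to the margin is 0.071 + 0.04 = 0.111. Power = Φ(2.803 − 1.960) = Φ(0.843) = 80%. The required n is 156.8, so 157 per arm, which is the stated figure. With the rounded 18%, power is 79.4% and n is 160. One-sided 5% at 11% vs 18% would need only 126 per arm, so it does not reproduce the plan.

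**Step 2: use the background multiplier (k = 2).** pO = 6% + 2% = 8%; pR = 10% + 3.1% = 13.1%. The variance sum is 0.0736 + 0.1138 = 0.1874, so SE is 0.0345. The distance to the margin is 0.051 + 0.04 = 0.091. Power = Φ(2.634 − 1.960) = Φ(0.674) = 75%. The required n is 177.7, so 178 per arm (356 evaluable, against 314). The lower event rates shrink the SE, which partly offsets the smaller gap; that is why the loss is about 5 points of power and no more.

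**Step 3: secondary sensitivity, perioperative stroke.** The comparator section's wording is below 2%, so 2% is the mildest reading.

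| OMT stroke, 2 years | Perioperative stroke | Later stroke, revascularisation arm | Power, k = 3 | Power, k = 2 |
|---|---|---|---|---|
| 3% | 3% | 2% | 80% | 75% |
| 3% | 2% | 2% | 57% (11% vs 15.1%) | 57% (8% vs 11.1%) |
| 2% | 2% | 2% | 87% (8% vs 15.1%) | 83% (6% vs 11.1%) |
| 2% | 2% | 1.33% | 75% (8% vs 13.1%) | 73% (6% vs 9.8%) |

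The last two rows also take medical stroke at 1% a year (2% over 2 years) from the same comparator section. That figure is for ipsilateral stroke in asymptomatic stenosis only, so applying it to the whole OMT arm is an assumption. In the last row, later stroke in the revascularisation arm is scaled by the same two thirds (2% × 2/3 = 1.33%), also an assumption.

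**The case against.** Several points on the other side are fair.

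- **The planning multiplier has references and the background remark has none.** The background remark is rounded and counts episodes, whereas the sample size counts patients. From the article alone, tripling cannot be called wrong. That stands. But the article does not use the distinction to explain the difference, so the two statements still need reconciling.
- **The power is stated conditionally.** The sample size section ties the 80% to its assumed rates and prints 11% and 18% beside it, so the 7-point advantage can be worked out. The Discussion warns that event rates may differ from those predicted and that the analysis may not settle the hypothesis. The initial analysis is also meant to inform a continuation or re-launch. This softens the risk of misreading. It does not tell the reader that the article already contains two different ratios.
- **The effect is modest.** A drop from 80% to 75% is small, and randomisation was suspended in October 2020.

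A reader might go further and infer that the article's own figures put power at 57%, because 3% perioperative stroke sits above the rate it cites for current practice. The documents do not support that. The lower figure is what most endarterectomy databases record. The 3% is a planning value for an arm that also allows stenting in selected cases, and the background says stenting carries higher early risk in symptomatic patients aged 70 or over. The 57% also comes from lowering that one input and leaving medical stroke at 3%, although the same section cites falls in medical stroke as well. Lowering both gives about 73–87%, depending on the multiplier and on later stroke after revascularisation. What remains is that the 3% is given without a reason, in a population that includes asymptomatic patients.

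**Conclusion.** The conflict over the multiplier is real and direct: total infarction is three times clinical stroke in one section and about twice in another. The stated 80% power holds under tripling. Under doubling it is about 75%, and 178 evaluable patients per arm would be needed in place of 157. This rests on the unpooled normal approximation and on the inferred one-sided 2.5%, which together reproduce the stated size exactly when the 0.1% death component is kept.

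This is a minor-to-moderate inconsistency in inputs. A reader might take it for an arithmetic error, but the sums within the sample size section are correct. The perioperative rate is a tension between a database figure and a planning value, worth a sentence of justification. The 57% at 2% is a one-input sensitivity result and should not be quoted as the trial's power.

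**What to change.** 1. Reconcile Background and rationale {6a} with Sample size {14} on one silent-to-clinical ratio. If tripling is kept, say why its sources outweigh the doubling statement, and amend the background.
2. If tripling cannot be justified, restate the power at 157 per arm as about 75%. Alternatively, give 75–80% across the two multipliers.
3. Say in words that 80% power assumes a true OMT advantage of about 7 points, and state the one-sided alpha used.
4. Add a sentence explaining the 3% perioperative stroke rate in light of the lower database figure in section {6b}. If a sensitivity figure is given (about 57% at 2%, other inputs unchanged), note beside it that the lower medical stroke rates cited in the same section offset the loss.
5. Carry the reconciled ratio into the sample size for any continuation or re-launch.

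The cost is a few sentences and a somewhat less favourable power statement. No extra patients, design change or change of analysis is involved.
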